## Discussion

The burden of CKM syndrome remains a major, yet increasing, challenge for healthcare systems worldwide [31]. In Germany, one of the key reasons are the low participation rates of population-based screening programs that aim to identify CKM syndrome risk factors [8]. Therefore, innovation for a more effective prevention is urgently needed.

The APOSCREEN-1 study investigates the potential of community pharmacies to help redefine preventive care strategies. A comprehensive dataset will be generated, capturing key metrics such as patient reach, acceptance and completion rates, as well as medical outcomes and pharmacist-reported applicability of the screening workflow. On this basis, primary outcomes were chosen to evaluate the overall applicability of the screening in community pharmacies, encompassing implementability, feasibility, and potential clinical benefit, which are key considerations for future scalability.

Our multi-parametric screening-approach will triage patients for further testing who are at significant risk for cardiovascular events or kidney disease while avoiding an overly low threshold for further work-up in order to maintain health care resource feasibility. Through this, the study is designed to address three central challenges of the German healthcare system:

First, a significant proportion of individuals remain excluded from prevention strategies due to logistical, social, and systemic barriers [32]. Primary care relies on voluntary check-ups, which limits general practitioners (GP) ability to reach those who do not attend medical practices. In contrast, the APOSCREEN-1 study proposes a widely accessible and frequently used care setting. By collecting screening data, the study will evaluate whether low-threshold screening in pharmacies may enhance access to screening.

Second, the incidence of CKM syndrome risk factors is increasing and a considerable number of medically underserved individuals can reasonably be assumed. Based on the obtained data, the APOSCREEN-1 study will enable the assessment of: (I) the prevalence of pathological findings in this at-risk population, (II) the proportion of individuals whose CKM syndrome risk factors remain untreated or insufficiently managed and (III) the number needed to screen for a previously unobserved risk factor (NNS) along with the positive predictive value of the PoC testing. As an exploratory endpoint, the study will assess whether pathological findings translate into changes in prescription and management by primary care providers.

Third, Germany faces an aging population with limited personnel resources [33–35]. Scalable, decentralized models are warranted. Community pharmacies are professionally staffed locations and well-positioned to support preventive care. Their increasing responsibilities in patient education, vaccination, and the use of diagnostic tools underline the health-serving potential. Feasibility analysis will provide insight into the applicability of a large-scale implementation and its challenges.

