### Inclusion and exclusion criteria

Eligible participants are adults aged 40 years or older who visit a participating pharmacy and meet at least one of the criteria summarized in Table 1. Recruitment of the pharmacies will be done sequentially over a 3-month period, starting from 1 April 2026. Each pharmacy will have 6 months to enroll 50 customers in the study.

**Table 1 Tab1:** Inclusion and exclusion criteria

Inclusion criteria	Exclusion criteria
Age ≥ 40 **and**	Participation in another study
Established regular GP **and**	Inability to give informed consent
Active smoking **or**	
Prescription of antihypertensive, antidiabetic, or lipid-lowering medication **or**	
Obesity (BMI ≥ 30 kg/m²; waist circumference ≥ 88 cm for women or ≥ 102 cm for men)	

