### Data source and collection at screening

In the initial visit, written informed consent will be obtained by the pharmacist and relevant data will be documented using an electronic case report form (eCRF). Table 2 displays the data collected at different time points. Subsequently, participants undergo standardized PoC assessments including albuminuria, blood pressure, HbA1c and full lipid profile (total cholesterol, non-high-density lipoprotein (non-HDL-C) cholesterol, HDL cholesterol (HDL-C), low-density lipoprotein cholesterol (LDL-C) and triglycerides). In pharmacies equipped for on-site PoC testing of albuminuria and blood pressure, all tests will be conducted at the initial visit. Alternatively, patients will be provided with validated home blood pressure monitors and semi-quantitative albuminuria tests along with instructions for testing. Results will be assessed in a second appointment in the pharmacy, together with PoC testing for HbA1c and lipid profile.

**Table 2 Tab2:** Data collected within the eCRF

Category	Data collected		
	At Screening	At Confirmatory Testing	At Follow-Up
Demographic data	• age • gender • postal code • educational level • employment status • type of health insurance		
History	• currently prescribed medication list • pre-existing medical conditions • family history of cardiovascular disease • smoking status • last participation in a health check-up		• medication • visits to the general practitioner after screening findings and therapy • changes from the GP visit • satisfaction with screening / self-assessed benefit of the project
Clinical	• home blood pressure (3x) • body weight • body height • calculated BMI • waist circumference	• 24-hour blood pressure	
Laboratory	• HbA1c • lipid profile (total cholesterol, non-HDL-cholesterol, calculated LDL, HDL, triglycerides) • albuminuria (albuminuria test or urine-albumin-creatinine-ratio)	• HbA1c • fasting plasma glucose • lipid profile (total cholesterol, LDL, HDL, triglycerides, lipoprotein(a)) • creatinine, cystatin c • urine-albumin-creatinine-ratio	

GP, General Practitioner; HDL, high-density lipoprotein; LDL, low-density lipoprotein, BMI, body mass index

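### The primary NNS pools newly found with poorly managed known risk factors, while the Discussion presents an NNS for unobserved factors and an access statement that no stated analysis supports

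*Protocol article*

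**What the plan says.** **What the NNS counts.** Under Primary outcomes (III), and again under Sample size and statistical analysis, the numerator event is one composite: at least one CKM risk factor that was unknown before screening or was known but insufficiently managed. The explicit definitions in Primary outcomes (III) are all worded for participants with known disease or existing therapy. NNS ≤ 5 counts as clinically meaningful, 5 to 10 as exploratory, and above 10 as unfavourable. The only NNS strata named are pharmacy-prompted versus self-referral recruitment.

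**What the Discussion says it counts.** The second of the three challenges lists as item (II) the proportion with untreated or insufficiently managed factors, and as item (III) "the number needed to screen for a previously unobserved risk factor (NNS", together with the PPV.

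**Who can enter.** Table 1 joins "Established regular GP" to the age criterion and to the risk criteria by "and". The risk criteria are alternatives: active smoking, "Prescription of antihypertensive, antidiabetic, or lipid-lowering medication", or obesity. The sentence above the table is looser ("meet at least one of the criteria summarized in Table 1"). Under Participant selection, flagged medication in the dispensing software triggers an invitation, and smokers and people with obesity may come forward themselves.

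**Access.** The first of the three challenges is that primary care cannot reach people who stay away from practices. It closes with the statement that "the study will evaluate whether low-threshold screening in pharmacies may enhance access to screening". Table 2 records "last participation in a health check-up".

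**The concern.** Items (II) and (III) in the Discussion treat poor control of known disease and detection of unobserved disease as two quantities. The statistical section produces one NNS that merges them. If the composite figure is reported under the Discussion's label, readers will take it as the number screened per newly found risk factor, which it is not.

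The entry criteria make the difference matter. Every participant has a GP, and some are invited because they already take a cardiovascular, antidiabetic or lipid-lowering drug. Part of the yield will be known disease above a control threshold. That finding is useful, but it supports a different policy from detection of undiagnosed disease. The Limitations section says the results will guide large-scale screening efforts and policy discussions.

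The access statement has a related gap. Its rationale is people outside regular care, the sample excludes anyone without a regular GP, and no listed outcome or stratum bears on access. The Limitations name selection bias and healthy-volunteer bias but not the GP requirement.

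**Working it through.** **1. The plan's own figures.** NNS ≤ 5 corresponds to a yield of 1/5 = 20%, as the text after the primary outcomes states. Planned size: 20 × 50 = 1000. Expected indications for testing at the study center: 10 × 50 × 0.50 = 250, of whom 250 × (1 − 0.20) = 200 complete it. All reproduce. None of them splits new from known factors.

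**2. Formula.** Let Y be the composite yield among completers and s the share of positive participants who have at least one previously unknown factor. Then

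NNS(composite) = 1/Y and NNS(new) = 1/(Y × s).

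NNS(new) exceeds 10, the plan's unfavourable band, whenever Y × s < 0.10.

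**3. Results.** The article does not give s, so it is shown as a range. Y = 20% is the success limit. Y = 50% takes the prevalence of risk factors expected in the sample-size section as if it were the composite yield, which is also an assumption.

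| s | NNS(new) at Y = 20% (composite 5) | NNS(new) at Y = 50% (composite 2) |
|---|---|---|
| 100% | 5 | 2 |
| 50% | 10 | 4 |
| 20% | 25 | 10 |
| 10% | 50 | 20 |

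At Y = 20%, NNS(new) is above 10 if s is below 0.10/0.20 = 50%. At Y = 50% this needs s below 0.10/0.50 = 20%.

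**4. Overlap.** The screening covers several parameters, so one person can have a poorly controlled known factor and a new one. Suppose 80% of participants are treated, 25% of these exceed a threshold for a known factor, and a further 3% of all participants have only a new factor (all assumed). The composite yield is 0.80 × 0.25 + 0.03 = 0.23, so the NNS is 4.3. The NNS for at least one new factor depends on how many of the 20% also have one:

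- none: 1/0.03 = 33
- one fifth: 1/(0.04 + 0.03) = 14
- half: 1/(0.10 + 0.03) = 7.7
- all: 1/0.23 = 4.3

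**5. Precision of a split.** The interval is 1.96 × √(p(1 − p)/n), inverted, with n = 1000 completers and clustering by pharmacy ignored.

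- p = 20%: half-width 2.5 points, 17.5% to 22.5%, NNS 4.4 to 5.7.
- p = 10%: half-width 1.9 points, 8.1% to 11.9%, NNS 8.4 to 12.3.

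The interval for the rarer component is wider on the NNS scale but still informative. For a table by last check-up, assumed shares of non-attenders of 10%, 20%, 30% or 50% of 1000 give half-widths at p = 0.5 of 9.8, 6.9, 5.7 or 4.4 points.

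**The case against.** The composite is deliberate. It is worded the same way in the abstract, the primary outcomes and the analysis text, and the 20% threshold is justified for it. Item (III) in the Discussion may be loose shorthand for that same NNS. This stands as a reason to keep the composite as primary. It does not remove the mismatch, because item (II) names insufficient management separately.

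Several stronger readings are tempting, and the documents do not support them:

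- *The plan cannot separate new from known factors.* It can. The Missing data section foresees classifying each factor as known, unknown, controlled or insufficiently managed, and history and medication are collected. The recruitment-route strata are a partial proxy. What is missing is a stated NNS that uses the classification.
- *Flagged prescriptions are the main recruitment tool, so the yield is mere re-measurement.* No route is ranked and no shares are given. Smoking or obesity allows entry without a prescription. A treated patient can have newly found albuminuria, raised HbA1c or raised non-HDL cholesterol, so an NNS such as 33 in step 4 of the working is only the upper end of a range.
- *The GP requirement shuts out people who skip check-ups.* Having a GP is not the same as attending check-ups, so non-attenders remain eligible.
- *The trial fails a stated access objective.* The stated aim is feasibility and diagnostic yield. Access appears only as a hedged sentence in the Discussion.

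Tables by check-up attendance are the kind of detail an article may leave to a full analysis plan that is not shown, so their absence is not counted as a defect. Likewise, whether the same bands should apply to each component is a matter of preference.

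**Conclusion.** The point holds as a mismatch between a primary outcome and the way the article describes it. The composite can meet NNS ≤ 5 while the NNS for at least one new factor lies anywhere from 5 to 50, for a new share from 100% down to 10%. At the limiting 20% yield it falls in the plan's own unfavourable band once fewer than half of positive participants have a new factor. At a 50% yield that needs fewer than one fifth.

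These figures rest on an assumed new share. They show what the composite leaves open and do not predict the result. The reading that a GP is compulsory follows Table 1; the looser sentence above the table should be brought into line with it. On access, the supportable conclusion is narrow: the statement can apply only to people with a regular GP, and no analysis described in the article currently backs it.

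**What to change.** Keep the entry criteria and the composite primary NNS, and change the following.

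1. Pre-specify next to the composite, each with a 95% confidence interval, the NNS for at least one previously unknown factor and the NNS for at least one insufficiently managed known factor, using the classification in the Missing data section. State that a participant may count in both.
2. Reconcile item (III) of the Discussion with Primary outcomes (III) and the statistical section, so that the composite is not reported as the NNS for unobserved factors.
3. Limit the access statement to people with a regular GP. If an access claim is made, base it on a descriptive table by last health check-up.

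This changes analysis and wording only. The variables are already in the eCRF, and no visit, entry criterion or sample size changes. The cost is wider intervals for the components and possibly a less favourable NNS for new detections.

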### Limitations

Participants receive an individualized, guideline-based risk report and recommendation tailored to the participant’s screening, nevertheless therapy induction relies on GP consultation. Currently, no universally accepted guideline-based NNS threshold exists for clinically meaningful detection efficiency. Instead, screening frameworks emphasize overall net benefit; for example, the United States Preventive Services Task Force does not use a fixed number needed to treat, screen, or harm as a decision threshold [20]. Therefore the NNS used reflects only a pragmatic approach. Due to the recruitment process, residual selection bias cannot be excluded, but will be mitigated through regular study monitoring during the recruitment phase. In addition, healthy volunteer bias may limit generalizability of patient-level findings, as participants opting into screening might be more health-conscious than the general population. Further, pharmacy-level selection bias cannot be excluded, as participating pharmacies were self-selected and may not be representative of all community pharmacies.

If APOSCREEN-1 demonstrates feasibility and sufficient diagnostic yield, a larger effectiveness study will be warranted. Such a follow-up trial could evaluate a scaled pharmacy-based screening approach in a more representative sample of pharmacies across Schleswig-Holstein and potentially additional German states, using health-insurance claims data to compare screened individuals with matched non-participants. Key outcomes should include GP-confirmed diagnosis of previously unknown or insufficiently managed CKM risk factors, initiation or intensification of guideline-based therapy, and, with longer follow-up, CKM-related hospitalizations or death.

In conclusion, APOSCREEN-1 addresses a timely and structural need to strengthen early CKM syndrome risk identification by leveraging community pharmacies. The findings will be essential to guide the development of large-scale screening efforts and policy discussions around integrating pharmacies into national prevention frameworks.

## Data Availability

Data will be shared with researchers who provide a methodically sound proposal. Individual deidentified data collected during the trial will be made accessible. Proposals should be directed to the corresponding author. Data requestors must sign a data access agreement to gain access. Data will be shared to achieve the aims in the approved proposal.

## Abbreviations

CKD: Chronic kidney disease
CKM syndrome: Cardiovascular–kidney–metabolic syndrome
CVD: Cardiovascular disease
eCRF: Electronic case report form
EU: European Union
GDP: Gross domestic product
GP: General practitioner
BMI: Body mass index
HBPM: Home blood pressure monitoring
HDL: C–high–density lipoprotein cholesterol
LDL: C–low–density lipoprotein cholesterol
NNS: Number needed to screen
NPV: Negative predictive value
PPV: Positive predictive value
PoC: Point–of–care
RASi: Renin–angiotensin–aldosterone system inhibitors
SGLT2i: Sodium–glucose cotransporter–2 inhibitor
SD: Standard deviation
TC: Total cholesterol
UACR: Urine albumin–creatinine ratio
